### Procedure

We employ three recruitment strategies. First, we distribute flyers on the university campus. Second, we post advertisements on Dutch websites for mental health issues. Third, advertisements are posted on Facebook and Twitter. The flyers and advertisements specifically target people who experience low mood or mood fluctuations and direct them to a website (www.moodmonitor.nu) that contains more detailed information. Interested individuals can apply to participate in the study via this website by completing the screening questionnaire (PHQ-9, age, possession of an Android-compatible smartphone), after which they can read the study information again and can agree to participate by entering a valid email address (electronic informed consent). Applicants who do not meet the inclusion criteria will be notified instantly. If they are excluded because they score above 15 on the PHQ-9, they are advised to contact their general practitioner. Participants who meet the inclusion criteria will be randomised equally to the three groups, i.e. 1:1:1. An independent researcher performs the allocation using a computerised random number generator. Next, participants are sent a link to the baseline questionnaire (CES-D, demographics), and participants in groups 1 and 2 receive an email with instructions to download and install the MoodMonitor app on their smartphones. Even though we do not notify participants directly as to which group they are randomised, they can find out easily by reading through the study information on the website, and therefore participants cannot be considered to be blinded. After week 6 and after week 12 participants in all three groups are sent an email containing a link to the questionnaires (CES-D at week 6, CES-D and SUS at week 12). Participants who complete a measurement are offered 7.50 Euro, i.e. 22.50 for all three measurements, and an additional 10 Euro if they respond to 80 % or more of the EMA prompts. Participants will receive this incentive in the form of an electronic gift voucher sent to their email address. We will continue recruitment until 160 applicants have been randomised. Data collection runs from April 2016 to November 2016. This trial’s results will be published on the study homepage when the scientific papers concerning the main objectives have been published.

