### Analyses

The primary outcome is the effect of EMA on depressive symptoms as measured by the CES-D at T6 and T12, comparing both EMA groups with the control group. To test this on all available data, we will conduct a mixed models repeated measures regression analysis, with T6 and T12 CES-D data as the dependent variable, and baseline CES-D scores, group (1, 2, 3), time (T6, T12) and the time*group interaction as independent variables. Effects will be expressed in terms of percentage of variance explained and Cohen’s d (by dividing raw regression parameter point estimates and confidence intervals by the pooled CES-D standard deviation).

For our secondary analysis, we will examine the EMA response rate over time, which gives an indication of response fatigue. Response fatigue will also be analysed by assessing response accuracy, here defined as a declining correlation over time between theoretically associated measures. Literature has shown that mood swings are associated with higher depressive symptoms [23]. Therefore, we will analyse the variance of the EMA and its correlation with the CES-D scores, taking into account the EMA ratings of the two weeks prior to the CES-D (i.e. weeks 5 and 6 for T6 and weeks 11 and 12 for T12). A decreasing variance of EMA ratings (i.e. increasingly stable responses) will result in a decreasing correlation coefficient (*r*) with the CES-D scores if the CES-D scores do not decrease. This might indicate a decline in validity.

We will maintain a family-wise two-tailed *p*-value of .05 using the Holm-Bonferroni method [24]. IBM SPSS Statistics 23 [25] and R [26] will be used for all analyses.

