### Sample size

For the sample size calculation, we assume that a difference between either EMA group and the control group within the margin −0.25< Cohen’s d <0.25 is clinically negligible. Therefore, a difference between groups of d = 0.25 should reach statistical significance in our analysis. We ran a power calculation in G*Power [27] for a repeated-measures analysis of variance (ANOVA), which is essentially the same analysis as linear mixed modelling when there are no missing values. A total number of 120 participants (40 per group) is required in order to obtain d = 0.25 with three assessment waves, a targeted power of .85, a significance level alpha of .05, and conservative estimations of correlations between measurements (*r* = .65) and variances of the differences between groups (non-sphericity correction epsilon = .8). Expecting 25 % drop-out at T12, we will recruit 160 participants. All participants will be included in the linear mixed model, which is robust for missing data.

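### The baseline CES-D is collected after unblinded randomisation and then used as the primary-model covariate, so allocation could shift it or whether it is returned

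*Protocol article*

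**What the plan says.** In the Procedure section, applicants complete an online screen (PHQ-9, age, phone) and consent. Then: "Participants who meet the inclusion criteria will be randomised equally to the three groups, i.e. 1:1:1". The baseline questionnaire comes after that step: "Next, participants are sent a link to the baseline questionnaire (CES-D, demographics), and participants in groups 1 and 2 receive an email with instructions" for installing the app. On blinding, the section says of participants and their group that "they can find out easily by reading through the study information on the website, and therefore participants cannot be considered to be blinded". Recruitment is counted at randomisation: "We will continue recruitment until 160 applicants have been randomised".

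The Analyses section specifies the primary model "with T6 and T12 CES-D data as the dependent variable, and baseline CES-D scores, group (1, 2, 3), time (T6, T12"), plus the interaction of time and group. Baseline CES-D is thus a covariate and not one of the modelled outcomes. The Sample size section adds: "All participants will be included in the linear mixed model, which is robust for missing data".

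Table 1 puts allocation and the first CES-D in the same column (t0) and marks both EMA rows from the t1-5 column onward.

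**The concern.** A baseline covariate is safe to adjust for because treatment cannot have affected it. Here that protection is missing. The score is self-rated, it is requested after allocation, and participants are not blinded. Groups 1 and 2 also receive an app-installation email that the control group does not get, which points to an EMA arm.

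This matters more here than in most trials, because the research question is whether assessment changes self-reported depression. The Limitations section itself accepts that a change in CES-D may reflect changed response behaviour. If allocation moves the T0 score, adjusting for that score moves the estimated effect.

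The second issue is who has a T0 score at all. A person can be randomised and counted in the 160 without ever returning the baseline questionnaire. A likelihood-based mixed model copes with missing outcomes, but a missing covariate is a different matter. If non-return differs by arm, the comparison is no longer between the groups as randomised.

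**Working it through.** **1. Order of events.** The Procedure section gives screening and consent, then randomisation, then the CES-D link to everyone and the app email to groups 1 and 2. Table 1 shows the intention that the CES-D (t0) precedes EMA (t1 onward). No sentence makes installation or the first prompt depend on a returned CES-D. According to the MoodMonitor section, week 1 has three ratings a day and participants may also enter ratings whenever they like.

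**2. Bias from a shifted covariate.** Let τ be the true follow-up difference (EMA minus control), b the within-group slope of follow-up on baseline, and δ the shift that allocation causes in T0 CES-D in an EMA arm, all in SD units. The adjusted contrast estimates

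τ − b × δ.

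Inputs:
- b = .65. This takes the correlation between measurements in the Sample size section as the slope, which assumes equal SDs at each wave.
- δ is not in the protocol. The values below are assumptions chosen to show the scale.
- The comparison value is the margin of 0.25 from the Sample size section.

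Results:
- δ = 0.05: .65 × 0.05 = 0.033 SD, 13% of the margin.
- δ = 0.10: .65 × 0.10 = 0.065 SD, 26% of the margin.
- δ = 0.15: .65 × 0.15 = 0.098 SD, 39% of the margin.

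If the slope were .5 or .8 instead, δ = 0.10 would give 0.050 or 0.080 SD. When δ has the same sign as τ the estimate is pulled towards zero. When the signs differ it is pushed away from zero. Nothing in the protocol fixes the sign.

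**3. The plan's own sample size.** The figure of 120 reproduces as a group-by-time interaction in repeated-measures ANOVA with 3 groups, 3 waves, f = 0.25/2 = 0.125, r = .65 and ε = .8:
- λ = 0.125² × 120 × 3 × .8 / (1 − .65) = 12.86
- df = 2 × 2 × .8 = 3.2 and 117 × 2 × .8 = 187.2
- power = 0.851

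Then 120 / (1 − .25) = 160. This figure is not in dispute here.

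**4. Missing baselines.** The share without T0 is not given. One extreme is that everyone without T0 is also absent at T12. The 25% allowance then already covers them, provided they are no more than 25%, and 120 remain. The other extreme is that T0 loss comes on top of 25% drop-out among the rest and no missing covariate is recovered:
- 5% missing: 160 × .95 × .75 = 114, power 0.830.
- 10% missing: 160 × .90 × .75 = 108, power 0.807.
- 20% missing: 160 × .80 × .75 = 96, power 0.752.

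These powers use the plan's own method. The percentages are assumptions.

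**The case against.** The strongest reply is Table 1. The documented schedule has no EMA at t0, so an app rating before the baseline CES-D would depart from it. The Procedure sentence also names two communications and does not say that they go out together. An article may leave to the full protocol whether the app waits for the questionnaire. This stands to the extent that a reader might infer that the plan has EMA start before baseline, and the document does not support that. It does not answer the point that allocation is known, or knowable, when the CES-D is completed.

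The sizes are also open to challenge. A shift of 0.10 to 0.15 SD at T0 would be 40% to 60% of the 0.25 effect that the whole trial targets, before any scheduled EMA. That is fair: the figures show leverage and do not predict the bias.

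A reader might further infer that everyone without T0 is lost, or that non-return will differ by arm. Neither is established. The Analyses section intends to use all available data. Imputation, or modelling baseline as an outcome, would keep these people in, and such handling may sit in an analysis plan that is not shown. Baseline completion is paid (7.50 Euro), and non-returners may largely be people the drop-out allowance already covers. What remains is that the model as written does not by itself deliver the promise to include everyone.

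**Conclusion.** The point holds as a design weakness with a risk of bias. The order of events, the lack of blinding and the covariate role are all stated in the article. An analysis plan could deal with missing T0 values, but it could not undo a shift in the values observed.

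The bias is about slope times shift and can go either way. With an assumed slope of .65 and assumed shifts of 0.05 to 0.15 SD, it is 0.03 to 0.10 SD against a margin of 0.25. The true shift is unknown and may be close to zero. It would be wrong to read this as showing that the baseline is contaminated, or that the EMA effect will necessarily be underestimated.

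On missing baselines, inclusion of all participants is not assured by the stated model, because recruitment is counted by randomisation and not by completed baseline. Any loss of power depends on how a missing covariate is handled and on how far T0 non-return overlaps with later drop-out.

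**What to change.** - Place the CES-D and demographics in the online application, after the PHQ-9 and consent. Randomise only when they are complete, send the app email afterwards, and count the 160 from that point. The sample size does not change.
- For anyone already enrolled under the present order, keep T0 CES-D as the primary covariate and add a sensitivity analysis adjusting for screening PHQ-9, which precedes randomisation and is known for everyone. PHQ-9 should not replace the CES-D in the primary model: it is a different instrument, restricted to 5 to 15 by eligibility, and would probably cost precision.
- Report by arm the number without T0 CES-D. For the EMA arms, also report when T0 was completed relative to the first app rating. App ratings are already time-stamped, so this needs only the questionnaire completion time.
- State how a missing T0 score is handled, so that the promise to include all participants can be kept.

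The cost is a slightly longer application and some applicants lost before randomisation instead of after it. If recruitment is under way, the web forms must be reordered mid-trial and the two enrolment periods kept distinguishable.

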### Instruments

Inclusion criteria will be determined using the Dutch version of the Patient Health Questionnaire (PHQ-9) [16], which will be administered online. The PHQ-9 contains nine items and covers nine criteria listed in the Diagnostic and Statistical Manual of Mental Disorders, 5th Edition (DSM-5), requiring respondents to rate the frequency of present difficulties during the past 2 weeks. Scores indicate the presence and severity of depression symptoms, with a maximum score of 27 and a minimum score of 0. Scores of 5, 10, 15, and 20 indicate mild, moderate, moderately severe, and severe depression, respectively. The internal consistency (Cronbach’s alpha) of the PHQ-9 with a clinical population was in the range of .86–.89 [17]. The instrument has shown good inter-format reliability between the original pen-and-paper and the online version [18]. We aim to include mild to moderately depressed participants, so we will include participants who score within the range of 5 to 15.

The primary outcome measure of this study is retrospectively measured depressive symptoms. We will use the Centre for Epidemiologic Studies Depression scale (CES-D) [15, 19] which will be administered online at baseline, after week 6 and after week 12. This scale consists of 20 self-rated items, each scored from 0 to 3. The total score ranges from 0 to 60, where higher scores represent more severe depressive symptoms. When used online, the CES-D has a good internal consistency (Cronbach’s alpha = .89–.93) and consists of 2 to 4 factors [20].

Several demographic variables (e.g. age, gender, educational level, marital status) will be gathered at baseline to determine the characteristics of the sample. We will also ask the participants how often and for which purposes they use their smartphones. At all measurement points participants are also asked whether they receive any professional help for mental health related problems, because that could influence their depressive symptoms.

The final questionnaire at week 12 contains the *System Usability Scale* (SUS) [21, 22] to evaluate the usability of the MoodMonitor app. Therefore the SUS will be administered to groups 1 and 2 only. The SUS comprises ten questions (e.g. ‘I would imagine that most people would learn to use this application very quickly.’) with five response options (ranging from ‘strongly disagree’ to ‘strongly agree’). Total scores range from 0 to 100, with higher scores representing higher usability. A SUS score above 70 could be considered adequate [22].

At the end of the study, we will randomly select ten participants in the EMA groups for a semi-structured interview by telephone to obtain qualitative information about: 1) their experience with tracking their mood and energy level; 2) their experience with the app and how it could be improved; 3) participation in this study in general (Table 1).

**Table 1 Tab1:** Schedule of enrolment, interventions and assessments

	Study period					
	Enrolment	Allocation	Post-allocation			
Time point	*-t* _*1*_	t0	*t1-5*	*t6*	*t7-11*	*t12*
Enrolment:						
Eligibility screen	X					
Online informed consent	X					
Allocation		X				
Interventions:						
EMA of mood			X	X	X	X
EMA of energy level			X	X	X	X
Control						
Assessments:						
PHQ-9, age, Android	X					
Demographics		X				
Use of smartphones, social media		X				
In mental health care?		X		X		X
CES-D		X		X		X
SUS						X
Interviews						X

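### The primary model adjusts only for baseline CES-D and leaves out the PHQ-9 screening score and professional help at T0, giving up a small gain in precision

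*Protocol article*

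**What the plan says.** Under Instruments, the protocol article explains why help-seeking is recorded: "participants are also asked whether they receive any professional help for mental health related problems, because that could influence their depressive symptoms". Table 1 schedules that question at t0, t6 and t12.

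The PHQ-9 has one stated role: "Inclusion criteria will be determined using the Dutch version of the Patient Health Questionnaire (PHQ-9"). Under Procedure, applicants apply "by completing the screening questionnaire (PHQ-9, age, possession of an Android-compatible smartphone"), so the score exists before allocation for everyone randomised, within the entry range of 5 to 15.

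Allocation is "randomised equally to the three groups, i.e. 1:1:1". The method is given as: "An independent researcher performs the allocation using a computerised random number generator". No stratification factor is stated. The baseline questionnaire follows allocation: "Next, participants are sent a link to the baseline questionnaire (CES-D, demographics"). The same section says that participants cannot be regarded as blinded.

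Under Analyses, the primary mixed model takes the T6 and T12 CES-D scores as outcome, with "baseline CES-D scores, group (1, 2, 3), time (T6, T12) and the time*group interaction as independent variables". The article states no analytic use for the help variable.

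**The concern.** The article lists the terms of its primary model, so this is a stated choice of covariates and not a detail left open. One variable is collected for a prognostic reason and then given no role. Another severity score, known before allocation, serves only as an entry filter.

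Recruitment mixes college students with users of mental health websites, and current treatment is not listed as an exclusion. With about 40 participants per group expected at T12, the share in care can differ between groups by chance. If people in care at T0 have a different course from people with the same CES-D score who are not, leaving the variable out puts that variation into the residual. What is at stake is the width of the confidence interval around contrasts that the article reads against a margin of 0.25 SD: "a difference between groups of d = 0.25 should reach statistical significance in our analysis".

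**Working it through.** **1. The plan's own figure.** Inputs from Sample size: d = 0.25, power .85, alpha .05, three waves, three groups, r = .65, epsilon = .8. A repeated-measures ANOVA for the within-between interaction with f = d/2 = 0.125 gives:

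- lambda = 120 × 3 × 0.125² × 0.8 / (1 − 0.65) = 12.86
- df1 = 2 × 2 × 0.8 = 3.2; df2 = 117 × 2 × 0.8 = 187.2
- power = 0.851, and the required N is 120
- 120 / (1 − 0.25) = 160

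The stated figures reproduce. The calculation contains no covariate, so leaving covariates out does not make it wrong.

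**2. What baseline CES-D already removes.** At one time point, adjustment at r = .65 leaves 1 − 0.65² = 0.5775 of the outcome variance, a cut of about 42%. With 40 per group, the SE of a pairwise contrast in d units is √(2 × 0.5775 / 40) = 0.170.

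**3. What the two covariates could add (assumed; no values in the document).**

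- PHQ-9: partial r = (b − 0.65a) / √[(1 − a²)(1 − 0.65²)], where a is its correlation with baseline CES-D and b its correlation with follow-up CES-D. For a of 0.6 to 0.7 and b of 0.4 to 0.55, partial R² is about 0 to 0.07. Example: a = 0.6, b = 0.5 gives 0.11 / 0.608 = 0.181, squared 0.033.
- T0 help: partial R² = p(1 − p)h² / 0.5775, where p is the share in care and h the difference in SD units given baseline CES-D. For p of 20% to 40% and h of 0.2 to 0.3, this runs from 0.0064 / 0.5775 = 0.011 to 0.0216 / 0.5775 = 0.037.

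A combined range of 0 to 0.10 covers nearly all of this.

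**4. Effect on the contrast.** The SE is multiplied by √(1 − partial R²). Power is for one pairwise contrast at one time point, d = 0.25, two-sided .05. It is a different test from the one in step 1 and serves only to show relative change.

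| Partial R² | SE (d units) | Fall in SE | Power, 40 per group | n per group for 85% |
|---|---|---|---|---|
| 0 | 0.170 | 0 | 0.306 | 166 |
| 0.02 | 0.168 | 1.0% | 0.312 | 163 |
| 0.05 | 0.166 | 2.5% | 0.320 | 158 |
| 0.10 | 0.161 | 5.1% | 0.334 | 150 |

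The SEs are before the cost of the extra terms. With 120 completers, three groups and baseline CES-D leave 120 − 4 = 116 error degrees of freedom, and two more terms leave 114. The cost is of the order of 2/114 = 1.8% of the variance, or 0.9% of the SE. At a partial R² near 0.02, cost and gain roughly cancel.

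**5. Chance imbalance is the same variance.** Take 30% in care and an effect of 0.4 SD, both assumed.

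- SD of the difference in share between two groups of 40: √(2 × 0.3 × 0.7 / 40) = 0.102
- Shift from a one-SD imbalance: 0.102 × 0.4 = 0.041 d
- Variance explained by help: 0.3 × 0.7 × 0.4² = 0.0336, and √(2 × 0.0336 / 40) = 0.041, the same number
- SE once that variance is removed: √(0.170² − 0.041²) = 0.165, a fall of about 3%

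The typical shift is already inside the unadjusted SE of 0.170. Adjustment takes it out once, as a reduction of about 3%.

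**The case against.** The strongest reply is that nothing here is an error. The article says that help could influence symptoms; it does not promise to adjust for it. Leaving out a prognostic covariate does not bias a randomised contrast, no stratification factor is being ignored, and the best expected predictor is already in the model. All of that stands, and it is why the point is minor. Further covariates are also often left to an analysis plan, but here the article lists the model's terms, so a recommendation to extend the list is fair.

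The second reply concerns timing. T0 help is asked after allocation, of unblinded participants, so it could be missing or coloured by knowledge of the group. This also stands. It does not separate T0 help from baseline CES-D, which comes from the same stage and is already in the model. It does not touch the PHQ-9, which is the cleaner of the two covariates.

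The third reply is that the PHQ-9 overlaps with baseline CES-D and is restricted to 5 to 15, so it may add almost nothing. That is possible, and the range above includes zero.

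A reader might infer more: that a typical imbalance of 0.041 d, or 0.041 / 0.25 = 16% of the margin, is a harm on top of lost precision. Step 5 of the working shows that it is the same variance counted again; its proper comparator is the SE of 0.170. A reader might also call the gain free. It costs two degrees of freedom, and T0 help may be incomplete.

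**Conclusion.** The point holds as a minor recommendation. The document gives a prognostic reason for recording help, holds a pre-allocation severity score for everyone randomised, and adjusts for neither. The loss is a fall in the SE of about 0% to 5% that is not taken up, before a cost of roughly 1% for the two extra terms. Power for a single pairwise contrast would rise from 0.306 to at most about 0.334. No conclusion of the trial is likely to turn on this.

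The size rests on assumed correlations for the PHQ-9 and an assumed prevalence and effect for help; the document supplies only r = .65. It does not support a claim of bias, of an invalid sample size, or of a separate harm from imbalance.

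**What to change.** In Analyses, add the PHQ-9 screening score as a fixed covariate in the primary mixed model, beside baseline CES-D. Add T0 professional help (yes/no) either as a further covariate or in a named sensitivity analysis. State that it is collected after allocation from unblinded participants, and how missing values will be handled. State that help at T6 and T12 will be described by group and not adjusted for, since it may itself respond to the assigned condition.

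The cost is a few lines of text, two degrees of freedom and possibly some missing T0 help values. No new data are needed. Under Data management, the researchers have no access to questionnaire data until collection is complete, so the covariates can be fixed before anyone sees outcomes. Adding help later would look like a post hoc choice.
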